### Measures

#### General questions and demographics

The demographic questionnaire for migrant patients (and confidants) includes the date, preferred language, name, (patient’s name, relationship to patient), mental health center of treatment, age at the time of admission, sex, age at arrival in the Netherlands, and country of origin. For migrant patients who were born in the Netherlands, the country of origin of both parents was included. In addition, the patient’s and parents’ level of education, patient’s occupation, profession, religion, level of religiosity, and previous diagnoses will be recorded. The clinician questionnaire includes the date, name, age, sex, country of origin, mental health center of work, profession, work experience in mental health, and prior experience or training in the use of the CFI.

#### The cultural formulation interview

The 16 semi-structured questions of the CFI serve as the intervention (10). The CFI aims to bridge cultural differences by explicitly asking about someone’s cultural background and its influence on the problems presented. Questions cover the cultural definition of the problem; cultural perceptions of its cause, context, and support; cultural aspects of coping; and past and present help-seeking behaviors. The informant version of the CFI (CFI-I), which will be used in consultations with confidants, consists of 17 questions covering the same topics. Clinicians schedule approximately one hour for the treatment sessions in which they use the CFI questions and context only with the patients in the intervention group. Clinicians are prompted to follow the outline of the CFI and CFI-I as provided in the DSM-5 (10). In the control group, these types of questions need to be avoided, whilst in both groups the necessary care will always be provided.

#### The cultural formulation interview fidelity check

The CFI fidelity check that is provided in the DSM-5 (28) will be used to verify compliance with the CFI questions in the intervention group and abstinence from the CFI questions in the control group. The fidelity check consists of 12 short, yes or no questions. The questions cover topics such as causes of the symptoms, severity of the symptoms, things that improve the symptoms, things that make symptoms worse, coping, identity, and past help-seeking behavior. It takes about five minutes to complete the fidelity check.

#### Working alliance

The main outcome indicating the strength of the therapeutic working alliance will be estimated using the Working Alliance Inventory (WAI) (29). The WAI consists of 36 items for clinicians and 12 items for migrant patients using a 5-point Likert scale. It takes clinicians approximately 10 minutes to complete the WAI online. Completing the WAI in person with the patients takes approximately 15 minutes. Available validated patient versions of the WAI are used in English, Dutch, Spanish, Turkish, and Arabic. In questions one and eleven of the Arabic WAI, the translation for the word indicating “problem” was changed because the Arabic word used in these two questions means “defect”, which has a negative connotation. The meaning of this word was independently checked by two native Arabic speakers, both of whom recommended that the word be changed to “problem”. Interpreters are used when translation into other languages is required, or when none of the researchers or experts by experience speaks the same language as a participating illiterate migrant patient.

#### Clinicians’ level of cultural empathy

The Scale of Ethnocultural Empathy (SEE) will be used to measure the clinician’s level of cultural empathy in the context of the previous treatment session(s) (30). The 31 items are scored on a 6-point Likert scale. For this study, three researchers independently translated the English SEE into Dutch. Differences in the translations were discussed until a consensus was reached. The scale measures four empathy factors: empathic feeling and expression (EFE), ethnocultural empathy awareness (EA), acceptance of cultural differences (AC), and empathic perspective-taking (EP). It takes approximately 10 minutes for clinicians to complete the questionnaire.

#### Perceived empathy

The Barrett-Lennard Relationship Index (BLRI) will be used to measure the perceived empathy of migrant patients and their confidants (31, 32). It was decided to use the validated 12-item version. Items are rated on a 6-point Likert scale. It takes approximately 15 minutes for the researchers to complete the BLRI together with the patients. Available validated versions of the BLRI are used in English, Dutch, Spanish, and Turkish. Interpreters are used when translation into other languages is required. **Table 1** shows an overview of the timing and the type of questionnaires for each participant group.

**Table 1 T1:** Overview of timing and type of questionnaire for each participant group.

After enrollment	After the first treatment	After the fifth treatment	After the consultation with the clinician	After the first treatment	After the fifth treatment
**All Participants**	**Patient**	**Patient**	**Confidant**	**Clinician**	**Clinician**
**Informed consent**	**BLRI-12**	**BLFI-12**	**BLRI-12**	**CFI Fidelity Check-12**	**CFI Fidelity Check-12**
**Demographic questions**		**WAI-12**		**SEE-31**	**SEE-31**
					**WAI-36**

Blue indicates the questionnaires for all participants that are administered by the researchers, Red indicates the questionnaires of migrant patients, Yellow indicates the questionnaire for confidants, and Orange indicates the questionnaires for clinicians.

### Data collection and management

A data management plan is available online at: https://dmponline.dcc.ac.uk/plans. The Tilburg University Qualtrics portal will be used for data collection. Data analysis, monitoring, and cleaning will be performed during and after the data collection. This process will be monitored by the research team, and the principal investigator will be blinded before the data analysis starts.

### Data analysis

Analyses will be performed using intention-to-treat principles. Missing data will be imputed using multiple imputation if assumptions are not violated. Non-parametric equivalents (Mann-Whitney U-tests) will be used when appropriate. All analyses will be performed taking into account the structure of the dataset (individuals within the four institutions: migrant patients, confidants, and clinicians). Data will be coded according to randomization.

Data analysis will be performed using SPSS-28. SEE, BLRI, and WAI scores will be calculated according to the instrument’s guidelines. Mean WAI scores between the intervention and control groups will be compared using t-test analyses. Linear regression analysis will be used to examine the main effect of CFI use on therapeutic working alliance and to test whether perceived empathy (BLRI and SEE) moderates (changes in strength and direction) the relationship between the use of the CFI and therapeutic working alliance when this relationship occurs. In addition, it will be tested whether perceived empathy (BLRI and SEE) mediates (explains) the relationship between the use of the CFI and working alliance within the framework of Baron & Kenny (33). **Figure 2** shows the to be examined moderating or mediating effect of perceived empathy in the analyses. To test for differences in the three analyses above, age, sex, generational status, country of origin, educational level, occupation, profession, religion, and religiosity of the migrant patients will be included as covariates or grouping variables in the analyses. In addition, the influence of gender differences among clinicians, work experience, and prior experience with the CFI will be explored.

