### Randomization

After enrollment, the migrant patients will be randomly assigned to the intervention or the control group by the principal investigator. During the data collection period, the data will not be fully anonymous, because the principal investigator needs to be able to plan appointments for data collection with both the migrant patients and clinicians and to avoid the risk of making mistakes in assigning the collected data to the correct participant ID in the main data file. Patients are single-blinded while their clinicians will be notified of the randomization status to use the CFI or adhere to standard care. Randomization will be set up based on the output of the online tool, Research Randomizer (26). Four groups, representing the four mental health centers and 100 participants per center, are entered into the tool. The resulting four sets of random order numbers, up to 100, are stored and used to randomize participants. Set 1 is used for GGZ Drenthe, 2 for Parnassia, 3 for CTP Veldzicht, and 4 for ProPersona. Odd numbers indicate the intervention group and even numbers indicate the control group. The order of the numbers defines the allocation to the respective participants in the order of inclusion. The same numbers are also used as ID numbers for the participants. The letters D, U, V, and P are added to the ID numbers to indicate the mental health center; D for GGZ Drenthe, U for Parnassia, V for CTP Veldzicht, and P for ProPersona. In addition, the letters MP for the main participant, C for clinician, and Co for confidants are added to the numbers to identify the role of the participants in the study. In this way, the number and treatment center letter link the participant to their clinician and confidant, making them anonymous but identifiable in their association. Before data analyses, the data file will be fully anonymized and the coding system changed by non-analyzing researchers to blind the researchers performing the analyses from knowing which participant was allocated to the intervention or the control group, and in which mental healthcare center they participated.

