The principal investigator will receive notice of the migrant patient’s fifth treatment session appointment with their personal clinician to schedule the second-stage questionnaire completion. The patients will have an in-person or online appointment where they will answer the same questions about perceived empathy, in addition to supplementary questions about the therapeutic working alliance. The questionnaires need to be completed within one week of the fifth session. After the completion of these questionnaires, the patient’s participation concludes. Subsequently, clinicians will conduct an online questionnaire after every fifth treatment session. This questionnaire includes the same fidelity check and empathy questions as offered after the first treatment session and additional questions regarding the therapeutic working alliance. Clinicians will continue treating other study participants and are required to reiterate the aforementioned protocol for each participating patient under their care. Their participation in this study will end after completing the questionnaires of their final migrant patient.

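### The t-test named for the WAI ignores the centre strata and shared clinicians that the plan promises to account for; the expected cost is lost precision, not false positives

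*Protocol article*

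**What the plan says.** The Data analysis section of the protocol article makes four statements that bear on this point:

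- A promise: "All analyses will be performed taking into account the structure of the dataset". A parenthesis explains the structure as patients, confidants and clinicians within the four institutions.
- The between-arm comparison: "Mean WAI scores between the intervention and control groups will be compared using t-test analyses". The fallback has no stated trigger: "Non-parametric equivalents (Mann-Whitney U-tests) will be used when appropriate".
- A second look at the same effect: "Linear regression analysis will be used to examine the main effect of CFI use on therapeutic working alliance".
- The covariates or grouping variables: "age, sex, generational status, country of origin, educational level, occupation, profession, religion, and religiosity of the migrant patients will be included". Clinician gender, work experience and earlier CFI experience are to be explored. Neither centre nor clinician identity is listed.

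No analysis is called primary. The Sample size section is worked out for a t-test on two independent groups.

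The structure itself is fixed elsewhere. Under Randomization, "Four groups, representing the four mental health centers and 100 participants per center, are entered into the tool", and each resulting list serves one centre, with odd numbers for intervention and even numbers for control. Under Data collection, clinicians "are required to reiterate the aforementioned protocol for each participating patient under their care". The section on the CFI has clinicians using it only with their intervention patients, so one clinician can have patients in both arms.

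**The concern.** Allocation is stratified by centre, and patients treated by the same clinician are likely to give more similar WAI scores than patients of different clinicians. A two-sample t-test or a Mann-Whitney test has no place for either fact, so the named tests cannot keep the promise made in the same section. The regression could keep it, but as described it does not. The result that decides the trial may therefore come from an analysis that leaves centre and clinician variation in the error term. The data file also matters: as the Randomization section describes it, a clinician's code is the patient's number plus a letter. That labels the patient-clinician pair, not the clinician across patients.

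**Working it through.** **1. The text.** The promise covers all analyses. The t-test and Mann-Whitney have no centre or clinician term, and the regression lists none. The promise is tied to no model.

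**2. The plan's own figure.** Inputs from the Sample size section: power .80, significance level .05 (sidedness not stated), difference .39, ratio 1, total 164. With .39 as the standardised difference d, n per arm = 2(z_alpha + z_power)²/d².

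- One-sided: 2(1.645 + 0.842)²/0.39² = 12.37/0.1521 = 81.3, so 82 per arm and **164** in total. This reproduces the plan.
- Two-sided: 2(1.960 + 0.842)²/0.39² = 15.70/0.1521 = 103.2, so 104 per arm and 208 in total.
- Two-sided power at 82 per arm: Φ(0.39·√41 − 1.960) = Φ(0.537) = .70.

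The two-sided baseline is therefore .70. Sidedness is a separate point and is used here only to fix the baseline.

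**3. Ceiling on the gain.** The documents give no variance shares and no number of clinicians, so these are assumptions. With total variance 1, centre share c and clinician share k, no model can do better than removing both at no cost. Power is then at most Φ(0.39·√41/√(1 − c − k) − 1.960). The last column of the table gives this ceiling.

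**4. Simulation.** Set-up: 4 centres × 41 patients = 164, 7 clinicians per centre (assumed), arms mixed within clinicians, two-sided .05, 1500 trials per case. The centre-plus-clinician model was fitted by generalised least squares with known variances, as a stand-in for the mixed model.

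| Centre / clinician share | t-test power | Centre + clinician model | Gain | Ceiling |
|---|---|---|---|---|
| .05 / .10 | .693 | .725 | .032 | .77 |
| .05 / .20 | .713 | .783 | .070 | .82 |
| .10 / .20 | .721 | .807 | .086 | .85 |

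The simulation error of one entry is about √(.7 × .3/1500) = .012. A repeat with separately written code gave .69, .71, .73 against .73, .79, .82. Adjusting for centre alone, with 5 clinicians per centre, gave .710 against .727 (shares .05/.10), .718 against .756 (.10/.20) and .730 against .799 (.20/.10).

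**5. Type I error under the documented design.** With clinician assignment unrelated to arm, the t-test's type I error was .048, .046 and .055 in the three settings of the table (3000 runs each). In the three centre-only settings it was .049, .045 and .038. Clinicians' patients are not strongly skewed to one arm: 41/7 is about 6 patients each, and for 6 patients with even odds the expected majority share is (2·6 + 12·5 + 30·4 + 20·3)/(64·6) = 252/384 = 66%. The simulated average was 66% to 67%, and the highest average in any one trial was about 76%.

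**6. What would raise it.**

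- *Strong skew.* With 85% of each clinician's patients in one arm, t-test type I error was .071 (clinician share .10) and .120 (.20), against .045 and .052 for the model.
- *A CFI effect that varies by clinician.* With slope variances of .05, .10 and .20, t-test type I error was .058, .068 and .089, and centre adjustment alone gave .063, .071 and .093. In another set of runs, a fixed-centre, random-intercept model gave .056, .063 and .089 against .052, .057 and .079 for the t-test. A random intercept alone does not cure this.

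**The case against.** Four things can be said for the plan.

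- *The regression could carry centre and clinician, and the details may sit in an analysis plan not shown.* This stands in part. Regression can hold both terms, and an article need not spell out a full model. But the article itself names the t-test, lists covariates without centre or clinician, and does not say which analysis decides. The conflict is within its own text.
- *Nothing is lost against the planned test.* This is true. The t-test power of .69 to .72 matches the .70 that 164 patients give two-sided. What is lost is precision that the design makes available.
- *The gain rests on assumed inputs.* This is also true. If the effect were half a standard deviation in the usual sense (d = 0.5), two-sided power would already be Φ(0.5·√41 − 1.960) = .89, with less left to gain.
- *Analyst blinding hides the centre.* This is no obstacle, because masked codes preserve both the blinding and the structure.

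A reader might go further and infer that ignoring clinicians inflates false positives, as it does in a cluster-randomised trial. The documents do not support that. Patients are randomised individually, clinicians can serve both arms, and the limitations section treats contamination of controls by trained clinicians as a risk. The 7% to 12% error rates need an 85% one-arm share that nothing in the article indicates. The Data collection section does not say how or when the personal clinician is chosen, so skew is not excluded. No passage indicates that the CFI effect varies by clinician either.

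**Conclusion.** The point holds as an internal inconsistency with a modest cost. The article promises analyses that respect the data structure, names tests that cannot do so, and leaves the primary analysis unnamed, while the sample size points to the t-test. Under the documented design, type I error should be about nominal or slightly conservative. The expected cost is roughly 3 to 9 power points, from a two-sided starting point of .70. That size rests on d = 0.39, 164 patients, assumed centre shares of .05 to .10 and clinician shares of .10 to .20, and 7 clinicians per centre. Inflated type I error is a conditional risk only. The change is worth making because it costs little, not because the t-test would be invalid.

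**What to change.** Name one primary, two-sided WAI analysis: a linear model of WAI on arm, with centre as a fixed effect and clinician as a random intercept. Use the same structure for the clinician-rated WAI-36 and for the regression and mediation models. Add a clinician-by-arm random slope as a sensitivity analysis, since the random intercept does not protect against an effect that differs between clinicians. Keep the t-test and Mann-Whitney as sensitivity analyses. Mann-Whitney should not replace the primary model, because it compares ranks rather than means and does not pool simply after the planned multiple imputation.

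Before the file is anonymised, give each clinician one code across all of that clinician's patients, and keep masked clinician and centre codes so that blinded analysts can fit the model.

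The cost is revised wording, slightly more analysis work and one extra coding column. No new data are needed, and the planned SPSS version can fit the model.

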It is hypothesized that this study will show that implementation of the CFI may have a positive, strengthening effect on the therapeutic working alliance between migrant patients and clinicians moderated by (perceived) cultural empathy. Therefore, the central research question of this study is: Does the use of the CFI influence the therapeutic working alliance between migrant patients and clinicians? In addition, it will be examined whether perceived cultural empathy moderates (changes strength and direction) or mediates (explains) the effect of CFI use on the therapeutic working alliance.

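### The Data analysis section puts the clinicians' own SEE ratings under perceived empathy, so a SEE result would be credited to patients' perception, which the SEE does not record

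*Protocol article*

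**What the plan says.** **Data analysis.** The variable under test is labelled "perceived empathy (BLRI and SEE". Linear regression is planned "to test whether perceived empathy (BLRI and SEE) moderates" the relation between CFI use and the alliance. The next step repeats the label: "it will be tested whether perceived empathy (BLRI and SEE) mediates (explains) the relationship", within the Baron and Kenny framework.

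**Clinicians' level of cultural empathy (Measures).** The SEE "will be used to measure the clinician’s level of cultural empathy in the context of the previous treatment session(s". The respondent is stated: "It takes approximately 10 minutes for clinicians to complete the questionnaire". Table 1 lists the SEE only in the clinician columns, after the first and fifth treatment sessions.

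**Perceived empathy (Measures).** The BLRI "will be used to measure the perceived empathy of migrant patients and their confidants". Table 1 places it with patients after sessions one and five, and with confidants after their single consultation.

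**Introduction.** The research question asks "whether perceived cultural empathy moderates (changes strength and direction) or mediates (explains) the effect" of CFI use on the alliance. The stated aim and the Figure 2 caption use the same construct. The section on benefits and consequences of participation lists it among the possible gains for patients in the intervention group. The Abstract speaks of perceived empathy without the cultural qualifier.

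**Randomization and Data collection.** Patients are blinded. Clinicians are told the allocation before treatment starts.

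**The concern.** The analysis gives one name to two measurements that differ in rater and in content. One is the patient's or confidant's view of the clinician. The other is the clinician's view of their own cultural empathy, given with knowledge of the arm. The hypothesis then uses a third name that combines the patient's perspective with the cultural content.

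What is at stake is the mechanism claim. The Abstract announces that the study will show whether the alliance is strengthened as moderated or mediated by perceived empathy. Suppose the SEE shows a path and the BLRI does not. Under the plan's wording that result counts as perceived empathy explaining the CFI effect, although it would show only how unblinded clinicians rated themselves. If the clinician version of the WAI is the outcome in such a model, the same person supplies both mediator and outcome after session five, and the label hides this.

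**Working it through.** No figure in the plan bears on this point, so the check is a cross-reading of each scale's rater, content and label.

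| | SEE | BLRI |
|---|---|---|
| Completed by (Measures, Table 1) | Clinician | Patient; confidant |
| About | The clinician's own level | Empathy as perceived by patient or confidant |
| Cultural content as described | Yes | None described |
| Rater knows the arm (Randomization) | Yes | Patients blinded |
| Heading in Measures | Clinicians' level of cultural empathy | Perceived empathy |
| Label in Data analysis | Perceived empathy | Perceived empathy |

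1. *Label against measure.* The last two rows agree for the BLRI and disagree for the SEE. The article assigns the SEE to a construct that its own Measures section reserves for another scale. It does so twice, once for moderation and once for mediation.

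2. *Hypothesised construct against measures.* Perceived cultural empathy needs a patient rater and cultural content. The BLRI has the rater, but no cultural content is described. The SEE has the content, but a different rater. No other empathy scale appears in Measures or Table 1.

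3. *Extent.* Two scales in two roles give 2 × 2 = 4 scale-by-role analyses. The mislabelling affects the SEE in its two roles, so 2 of the 4. The comparison of mean WAI scores by t-test uses neither scale.

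That the SEE is self-report is an inference, but a direct one: clinicians complete a scale of the clinician's own level.

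**The case against.** **A loose umbrella term, not an error.** Data analysis names both scales each time, and the Measures headings and Table 1 show who rated what. Nothing says the scales will be pooled, and separate models may already be intended in a plan that is not shown. This stands in part: correct reporting remains possible, and misreporting is an inference from the label. But the article fixes the label itself, and that label contradicts its Measures section. A later plan that follows it would carry the contradiction forward.

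**Perceived cultural empathy may be measured after all.** The BLRI items are not shown, and a migrant patient rating a clinician's empathy is doing so in a cross-cultural setting. This also stands in part. The statement that no scale measures the construct holds only as far as the scales are described.

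**Two stronger readings that a reader might infer.** The first is a false-positive rate for four tests of one claim: 1 − 0.95⁴ = 0.185. The plan does not support that figure. Moderation is to be examined only where a relation between CFI and alliance is found. Baron and Kenny mediation is stepwise. The tests share patients and outcome, and moderation and mediation are distinct questions. If both are gated on a main-effect test at 0.05, the chance of any false claim when nothing is true is at most about 5%. Separate models would in any case leave the number of tests unchanged.

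The second is that the SEE is at fault because it can respond to delivering the CFI. For a mediator that is required. For a moderator it is a weakness, but the BLRI shares it, since it is first measured after session one. Measurement of moderators after randomisation is a separate issue. Moving the SEE to the clinicians' pre-enrolment form would not settle it: the SEE is framed around preceding sessions, one score per clinician would replace patient-specific scores, and that form precedes the CFI training.

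**Conclusion.** The point holds as a mismatch between construct and label. The article tests a clinician-completed scale of the clinician's own cultural empathy under a name that its Measures section gives to the patient and confidant scale. Its hypothesis names a construct that, as the scales are described, neither measures. A SEE finding reported under that label would support a claim about perception that no patient rated.

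The size is limited: the SEE analyses in both roles and the wording of the mechanism conclusion. The primary WAI comparison and the data to be collected are unaffected. The conclusion rests on the descriptions in Measures and Table 1, and on reading the SEE as self-report. It does not rest on any multiplicity calculation or on the timing of the SEE.

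**What to change.** - In the Introduction (aim, hypothesis and research question), the section on benefits and consequences of participation, Data analysis and the Figure 2 caption, confine perceived empathy to the BLRI as rated by patients.
- Analyse the SEE in separate models labelled clinician self-reported ethnocultural empathy.
- State a separate conclusion for each scale, so that a SEE result is never offered as evidence of what patients perceived.
- Draw no conclusion on perceived cultural empathy.

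The cost is rewording and separate model specifications, with no new data or visits. It can be done before the blinded analysis begins. The downside is a narrower claim about mechanism.
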